## Abstract

**Background:**

Since many individuals who initiate physical activity programs are highly likely to return to a sedentary lifestyle, innovative strategies to efforts to increase the number of physically active older adults who successfully *maintain *beneficial levels of PA for a substantial length of time are needed.

**Methods/Design:**

The Keep Active Minnesota Trial is a randomized controlled trial of an interactive phone- and mail-based intervention to help 50–70 year old adults who have recently increased their physical activity level, maintain that activity level over a 24-month period in comparison to usual care. Baseline, 6, 12, and 24 month measurement occurred via phone surveys with kilocalories expended per week in total and moderate-to-vigorous physical activity (CHAMPS Questionnaire) as the primary outcome measures. Secondary outcomes include hypothesized mediators of physical activity change (e.g., physical activity enjoyment, self-efficacy, physical activity self-concept), body mass index, and depression. Seven day accelerometry data were collected on a sub-sample of participants at baseline and 24-month follow-up.

**Discussion:**

The Keep Active Minnesota study offers an innovative approach to the perennial problem of physical activity relapse; by focusing explicitly on physical activity maintenance, the intervention holds considerable promise for modifying the typical relapse curve. Moreover, if shown to be efficacious, the use of phone- and mail-based intervention delivery offers potential for widespread dissemination.

**Trial registration:**

ClinicalTrials.gov Identifier: NCT00283452.

## 1. Background

Despite substantial data documenting the health benefits of physical activity [1-18], sedentary behavior remains a significant public health problem that is particularly prevalent among older adults. The 2005 Behavioral Risk Factor Surveillance System (BRFSS) documents that among adults age 45–54, more than half (52%) were obtaining less than recommended levels of physical activity, with the same being true for 55% of adults age 55–64 [19]. With a few exceptions [20,21], most intervention efforts have remained focused on PA initiation [22-32]. However, since ongoing participation in PA is necessary to sustain health benefits, complementary strategies to increase the number of sedentary individuals who *initiate *PA and efforts to increase the number of physically active individuals who successfully *maintain *beneficial levels of PA for a substantial length of time are needed. The importance of focusing attentions specifically on maintaining PA, is underscored by reports that roughly half of older adults who initiate a program of PA discontinue within three months [11]. These data, coupled with the observation that prevalence of sedentary behavior increases with age [19] suggests that population levels of PA may be substantially increased by preventing currently active individuals from falling below recommended levels of physical activity. More programs are needed for older adults that focus on maintenance, incorporate moderate intensity PA and are simple, convenient to engage in, relatively inexpensive, and noncompetitive [13].

Lack of data on the efficacy of low-cost interventions that have high penetration into target populations remains a hurdle to widespread dissemination of population-based interventions to increase levels of PA. The Keep Active Minnesota project addresses this need. Several aspects of our intervention should increase its efficiency and credibility, relative to other interventions, making it uniquely suited for widespread dissemination. First, by employing a phone- and mail-based strategy of intervention outside of the clinical setting, we do not add a burden to primary care providers. Second, by focusing on the older adult population, we target those at ages where maintenance of physical activity may yield particularly large benefits in terms of disease prevention and health improvement. Third, by supporting PA maintenance among recently active older adults, we are targeting individuals during a life-course stage where they are at increased risk for becoming sedentary. Fourth, those who have self-initiated a recent increase in physical activity have signaled their willingness and interest in maintaining healthy behaviors, which may make them more adherent to behavioral recommendations. Finally, because maintenance efforts may require fewer resources than interventions promoting initiation, the overall resource demands and per-unit costs of delivering our program should be lower than comparable initiation programs.

We address this research gap by evaluating the efficacy of a population-based approach to promoting PA *maintenance *among 50–70 year old adults who recently increased their physical activity level. The primary goal of the Keep Active Minnesota study is to assess the extent to which an interactive phone- and mail-based intervention helps participants maintain the level of activity they reported at baseline, over a period of two years in comparison to usual care. This paper describes the design and baseline data of the ongoing Keep Active Minnesota physical activity maintenance trial.

## 2. Methods

### 2.1 General design

The goal of Keep Active Minnesota was to recruit members of a large managed care organization (HealthPartners, hereafter HP) who had recently increased their physical activity level outside of a formal research study, and randomize them to one of two study groups: a telephone- and mail-based intervention designed to promote physical activity maintenance and a usual care control group who will not receive any physical activity intervention or advice beyond what is typically provided to health plan members. Absolute level of physical activity and maintenance of physical activity, defined as physical activity level relative to baseline, are the primary study outcomes. Figure 1 depicts the CONSORT diagram for the trial.

**Figure 1 F1:**
[figure not shown]
CONSORT diagram to describing flow of participants through the trial.

### 2.2 Recruitment and screening

The goal of recruitment was to obtain baseline data from 1,000 male and female HP members ages 50–70 who were eligible and interested in participating in the intervention study. A two-phase recruitment process was used. In the first phase, a sampling frame of 104,000 HP members was identified using administrative data and the eligibility criteria described below in the eligibility section. In mid July 2004, a screening survey was administered by mail to a random sample of 4,000 age-eligible individuals, to provide data to characterize the population from which the intervention sample was being recruited. These individuals received a letter describing the study and a six page survey which we use elsewhere (manuscript in preparation) to assess similarities and differences between study enrollees and the sampling frame from which they were recruited. This survey also included a brief set of eligibility screening questions. Participants who completed the survey and met eligibility based on PA criteria were called, received information on the second phase of the study and were asked if they were interested in participating.

In the second phase, recruitment proceeded both via direct mail recruitment starting in December 2004, and via self-referral, starting in March 2005. For the direct mail recruitment efforts, a cover letter similar to that used in the first recruitment phase was sent; no survey was included, however, the back of the cover letters contained several brief screening questions to determine eligibility and interest. Recipients were asked to answer these questions and return them. Upon receipt of these screeners, eligible participants who indicated interest in the study were contacted by phone. Two strategies were implemented to increase representation of racial/ethnic minorities in the study population. First, direct mailings of invitation letters and eligibility screeners were sent to all age-eligible health plan members who were identified as racial/ethnic minorities in the HP administrative database. Because collection of information on race/ethnicity had only recently started in the health plan, the number of potentially eligible individuals so identified was only about 2,100 out of an age eligible pool of roughly 104,000. Second, geographically targeted direct mailings were conducted to more than 2,000 age-eligible health plan members who reside in census tracts in which minority individuals are over-represented (>= 40% racial/ethnic minorities, based on Census 2000 counts). These strategies were completed in the first four direct mail waves, ending in March of 2005.

The final two waves of direct mailings were targeted to eligible health plan members who had engaged in one of two health plan programs that promote physical activity. In May, mailings were sent to participants in a program that pays a rebate to health plan members who visit participating health clubs a minimum of eight times per month. In July, mailings were sent to health plan members who participate in a mail and web based physical activity program that uses a pedometer.

As a third method of recruitment, inexpensive forms of advertising were used to generate "self-referrals" to intervention staff who conducted phone-based, real-time eligibility screening of interested individuals. Brief descriptions of the study and eligibility criteria were placed in a variety of print, email and web media. Venues included a health newsletter that is sent to all HP members; the HP and HealthPartners Research Foundation (HPRF) web sites; an electronic newsletter to HP employees; posters and brochures at all metropolitan YWCA's and YMCA's; a targeted email from a large employer to all age eligible employees with HP insurance; and two other large employers included the descriptions of the study in electronic newsletters to employees.

To be eligible, participants had to be between the ages of 50–70 years old, enrolled in the health plan for at least 11 of the 12 months prior to screening for study eligibility, and have increased their physical activity level either on their own or with the support of a program during the past year to a minimum of 30 minutes of moderate or vigorous PA a day at least 2 days per week on average over the past four weeks. The minimum of two days per week of moderate intensity PA is a clinically relevant cutoff, since regular PA at this level has been shown to generate significant improvements in functional capacity, fasting insulin levels, and other health-related variables [33-35] and to reduce risk of Type 2 diabetes in women [36]. Participants were excluded if they had a modified Charlson comorbidity score > 3 (a standard index of comorbidity calculated using prior year diagnoses of a broad range of serious medical conditions) [37,38], or had diagnoses of coronary heart disease (CHD), congestive heart failure (CHF), atrial or ventricular arrhythmias, cardiac arrest, or had an implantable defribillator.

Regardless of recruitment method, all potential participants were contacted by telephone to confirm their interest in study participation and to conduct an initial consent discussion. Following this discussion, consent forms were mailed to interested individuals who were asked to read, sign, and return a consent form. The consent form was reviewed and approved by the Regions Hospital Human Subjects Review Board. When completed consent forms were received a baseline telephone interview (see Section 2.7 below) was scheduled with the participant.

### 2.3 Randomization

Upon completion of the baseline telephone interview, participants were randomized by the study coordinator as they enrolled according to a schedule pre-determined by the study statistician and unobservable to the staff conducting randomization, based on a random number table embedded in the backend of the recruitment tracking database. Blocks of 20 were used to maintain study arm balance throughout the recruitment period. 1,049 subjects were randomized either the PA treatment condition (KAM) or a usual care control group (UC).

### 2.4 Intervention background

PA is a complex behavior with multiple determinants and pathways to change [39,40]. Historically, behavior change theory, research and intervention have primarily focused on initiation as opposed to maintenance. However, the importance of behavior change maintenance and the recognition that mechanisms underlying maintenance likely differ from those underlying initiation have been receiving increased attention in recent years. Three perspectives relevant to PA maintenance that inform our intervention include the Transtheoretical Model (TTM) [41-43], Rothman's theory regarding differential decision criteria for initiation versus maintenance [44], and the relapse prevention model [45]. We also look to the extensive literature on behavioral determinants of PA and activity maintenance to develop our intervention focus. Finally, since no single theory encompasses all factors related to PA maintenance [46] we use social cognitive theory (SCT) [47] as an organizing framework. Given its multidimensional emphasis on personal, behavioral and environmental factors, SCT provides a useful framework for accommodating the complexity of factors thought to influence PA maintenance.

Key constructs relevant to PA maintenance, depicted in Figure 2, include self-efficacy, perceived benefits of PA, coping skills for dealing with lapses, social support, and access-availability of PA opportunities. These measures provide an opportunity to gain insight into mediating factors associated with PA maintenance, an important, but understudied component of behavior change research [48,49].

**Figure 2 F2:**
[figure not shown]
SCT-based Conceptual Model for PA Maintenance.

### 2.5 KAM intervention description

Participants randomized into the intervention were offered an interactive telephone and mail-based physical activity support program. After randomization, participants assigned to the intervention arm were invited to attend an in-person orientation to the study. Sessions started in October of 2004 and ended in November of 2005. There were a total of 13 sessions and attendance ranged from approximately 10 to 50 participants per session. During the orientation participants were introduced to the study staff, received information on the study's goals and procedures, picked up their study materials and, when possible, made an appointment for their first session with the phone coach. Approximately two-thirds of intervention study participants attended the in-person orientation. Those unable to attend in person were received their study materials via mail and took part in a phone based orientation with one of the activity coaches.

The core component of the intervention was a seven session course delivered over the phone by activity coaches with a background in exercise science and training in behavior change theory. Each course workbook session included topics to be covered during the phone coaching session, instructional material, assignments for participants to work through on their own and goal setting. Participants were encouraged to use their pedometer to monitor their physical activity, however, they could also choose to self-monitor their physical activity in whatever way would be useful to them (e.g., minutes, miles). Course session topics included: the benefits of physical activity; goal setting and the development of an action plan; a discussion of types of physical activity and exercise; overcoming barriers to physical activity, problem solving and enhancing self-efficacy; social support; healthy eating; relapse prevention; and developing an action plan for long term maintenance.

The sessions were scheduled at the participant's convenience, designed to last about 20 minutes, to take place about twice a month and to be tailored for individual participants.

The course sessions were set up so that goals from the last session were initially reviewed along with any questions or concerns about previous topics. Then the topic of the session along with the accompanying homework was discussed. Activity coaches provided feedback and encouragement, helped with problem solving and encouraged the participant to revise their physical activity goals, if needed.

Following completion of the course, participants receive monthly follow-up calls for the remainder of the first year of study participation and then bi-monthly calls for the second year. Additional intervention components include motivational challenges, group sessions, and a lending library of physical activity resources.

Intervention participants were invited to engage in three motivational challenges during the course of their time in KAM. The challenges were designed to support the course objectives and timed to occur at six month intervals, with the first challenge starting soon after the subject finished the bi-weekly phone course. At the start of the challenge, participants were sent a flyer describing the challenge and a tracking form to document contest participation that could be mailed in a provided envelope before the contest deadline. Participants were also encouraged to share a story about lifestyle behavior changes they had made related to the challenge. The challenge topics were cross-training, tracking healthy eating and stress reduction strategies and taking a virtual walk to a popular and well-known Minnesota destination, via pedometer or minutes walked; the numbers of participants who engaged in each challenge were 91, 118 and 156, respectively.

Small prizes were offered for individual participation, for the "wave" (defined by the month the participant completed their in-person or phone orientation) with the most participants and for the individual submitting the most engaging story. At the end of each challenge time period, a newsletter was sent that announced the winners in each category. The newsletter also contained the winning story, a profile of a KAM participant as well as a profile of a KAM study team member and a list of physical activity opportunities in the Twin Cities metro area for the next six months.

If subjects wanted to try a new type of exercise or were in need of motivation, they were offered resources from a physical activity toolbox, a lending library of books, videos and DVD's. During the course of the study more than 70 items were mailed to subjects.

Four different group sessions featuring outside guest-speakers were offered during the second year of the study. A majority of study participants were still active in the study at that time. The sessions were designed to offer advice and support in a different venue than the course. Session topics included sports medicine, healthy eating, staying active in the winter and bicycling. Attendance varied with the topic and season, but approximately 50 subjects, on average, attended each group session.

### 2.6 Usual care description

Participants randomized into the Usual Care (UC) condition received information about the 10,000 steps physical activity program offered by the healthplan after their baseline phone survey and 4 newsletters focused on general health and wellness during their two years of study participation.

### 2.7 Measurement

All primary and secondary outcome measures were collected during a 45 minute telephone interview scheduled at a participant's convenience and administered prior to randomization, and 6, 12, and 24 months later. Participant responses were recorded by the interviewer onto an optically scan-able form that was scanned following administration, so that data were immediately available in the main study database.

### 2.8 Primary and secondary physical activity outcomes

The primary outcome measures for this study are kilocalories expended per week on a range of activities (total kcal/wk) and kilocalories expended per week on a subset of moderate and vigorous activities (moderate kcal/wk). Both kcal expenditure measures are computed using the CHAMPS instrument, designed for use in adult populations such as this one to assess the self-reported frequency and duration of a range of common activities and convert these reports into weekly kcal expenditure [50]. The CHAMPS instrument has demonstrated acceptable reliability with ICCs for moderate intensity activities of 0.67, 0.76, and 0.81–0.88 at six months, two weeks, and one week, respectively. Higher intensity activities demonstrate more modest ICCs of 0.66, 0.62, and 0.34–0.45 at six months, two weeks, and one week, respectively [51,52]. The instrument has also demonstrated adequate discriminate and construct validity, correlates well with other measures of physical activity and is sensitive to change [52].

Sample size was based on that which would be needed to detect a time (24 month vs. baseline observation) by treatment (KAM vs. UC) interaction at .80 power (two-tailed, alpha = 0.05) on the total kcal/wk variable in a two group repeated measures ANOVA. We assumed a common standard deviation of 1500 kcals/wk at each of 4 time points and a first order autoregressive residual covariance structure. These parameters suggested that N = 349 per study arm would be needed to detect the interaction of primary interest. Assuming non-differential 70% retention across study groups, we recruited N = 500 per arm.

Additional PA outcomes assessed include whether participants maintained PA at the follow-up measurement points, defined as moderate kcal expenditure at least 1500 kcal/wk and at least 80% of that expended at baseline and whether participants met CDC/ACSM physical activity recommendations of 30 minutes of moderate activity 5 or more days per week (moderate); 20 minutes of vigorous activity at least 3 days per week (vigorous); and moderate or vigorous activity recommendations [53]. A randomly selected sub-sample of enrolled study participants (50 from each treatment group) had their PA monitored via the MTI Actigraph (Manufacturing Technologies, Inc. Fort Walton Beach, previously referred to as the Computer Science and Applications (CSA) Monitor) at baseline and 24 month follow-up. Body mass index (BMI; kg/m^2^) was calculated from baseline and 6 month self-reported weight and baseline height.

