## 3. Results

Table 1 shows participant characteristics and physical activity level according to recruitment source; direct mail and self-referral. Participants who responded to a direct mailing about the study were less likely to be female and more likely to report "fair" or "poor" health status compared to those who self-referred themselves into the study after learning about the study through print, email or web media advertisement. No other statistically significant demographic or baseline physical activity characteristics differentiated direct mail and self-referral participants.

**Table 1 T1:** Participant Characteristics and PA as Mean and Standard Error or Percent by Source of Recruitment

	Direct Mail	Self-Refer	All
N	824	225	1049

age at baseline	57.1(.18)	57.2(.34)	57.1(.16)

female	69.5	82.7***	72.4

BMI, kg/m^2^	27.6(.19)	27.5(.38)	27.6(.17)

White	94.2	97.3	94.9

Hispanic/Latino	1.9	1.8	1.8

employed full time	76.2	79.1	76.8

4 year degree or more	66.3	68.4	66.7
			
functional health status fair or poor	7.0	3.1*	6.2

kcal/wk,	4721	4679	4712
total	(91)	(155)	(79)

kcal/wk,	2837	2731	2815
moderate or vigorous	(72)	(125)	(63)

moderate activity	23.5	28.4	24.6
30 minutes, 5/week			

vigorous activity	35.7	36.4	35.8
20 minutes, 3/week			

moderate or vigorous	48.8	55.1	50.1

* self-refer vs. mail, p < .05

*** self-refer vs. mail, p < .001

As documented in Table 2, at baseline the typical participant was about 57 years old, female, White, overweight (BMI ≥ 25 kg/m^2^), working full time, and college educated. Few participants reported fair or poor functional health status. Randomization successfully resulted in study groups that were similar on most demographic, physical activity, and psychosocial characteristics. The only observed demographic difference between the groups was that fewer KAM participants self-identified as White (95.6 vs. 92.4%, p < .05). Participants assigned to the KAM group were less likely to report engaging in moderate physical activity a minimum of five times per week, but reported higher levels of social support for physical activity from family members.

**Table 2 T2:** Participant Characteristics and PA as Mean and Standard Error or Percent by KAM and Usual Care Groups

	UC	KAM	All
N	526	523	1049

age at baseline	57.1(.22)	57.1(.22)	57.1(.16)

female	71.8	72.9	72.4

BMI, kg/m^2^	27.7(.24)	27.5(.23)	27.6(.17)

White	96.2	93.5*	94.9

Hispanic/Latino	1.2	2.5	1.8

employed full time	76.6	77.1	76.8

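### The sample size assumes an SD of 1500 kcal/wk for total expenditure, but the article's own baseline standard errors imply about 2,560; at the planned effect and correlation, 80% power becomes about 38%

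*Protocol article*

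**What the plan says.** Section 2.8 powers the trial to "detect a time (24 month vs. baseline observation) by treatment (KAM vs. UC) interaction", with two-sided alpha 0.05 and power 0.80, on total kcal/wk. The variance inputs are "We assumed a common standard deviation of 1500 kcals/wk at each of 4 time points" and "a first order autoregressive residual covariance structure". The result is given as "These parameters suggested that N = 349 per study arm would be needed to detect the interaction of primary interest", followed by "Assuming non-differential 70% retention across study groups, we recruited N = 500 per arm". The section gives neither the difference in kcal/wk to be detected nor the value of the autocorrelation.

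Section 3 then reports baseline data. Table 2 is titled "Participant Characteristics and PA as Mean and Standard Error or Percent by KAM and Usual Care Groups", so the bracketed figures are standard errors. For total kcal/wk it shows 4781 (114) for UC, 4643 (109) for KAM and 4712 (79) overall, with n = 526, 523 and 1049. Table 1 shows 4721 (91) for 824 direct-mail participants and 4679 (155) for 225 self-referrals. The article does not compare this spread with the planning SD.

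**The concern.** A standard error of 79 in 1,049 people cannot come from a variable with an SD of 1500; that SD would give 1500/√1049 = 46. The planning SD was meant to apply at every visit, including the one already measured, so the article contradicts its own sample-size input. Sample size rises with the square of the SD, so a ratio of 1.7 matters.

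Total kcal/wk is one of the two primary outcomes. The 80% is the only power figure in the article, so a reader of a null 24-month interaction would naturally set the result against it. The trial may be much less able to detect its planning effect than that figure suggests.

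**Working it through.** **1. The plan's own figure.** N = 349 cannot be reproduced, because the effect and correlation are not stated. The retention step can: 349/0.70 = 498.6, which agrees with the 500 per arm recruited.

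**2. Baseline SD from the tables, SD = SE × √n.**

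| Group | SE | n | SD |
|---|---|---|---|
| UC | 114 | 526 | 2,615 |
| KAM | 109 | 523 | 2,493 |
| All | 79 | 1049 | 2,559 |
| Direct mail | 91 | 824 | 2,612 |
| Self-referral | 155 | 225 | 2,325 |

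Rounding of the SE moves the overall value only between 2,542 and 2,575. The same conversion gives 0.16 × √1049 = 5.2 years for age and 0.17 × √1049 = 5.5 kg/m² for BMI. Both are sensible, so the brackets are indeed standard errors. The ratio to the planning value is 2559/1500 = 1.71; the variance ratio is 2.91.

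**3. Power with effect and correlation held as planned.** Let r be the baseline-to-24-month correlation and n the number per arm. With a common SD, the between-arm difference in change has variance 4·SD²·(1−r)/n. At 80% power the effect is 1.960 + 0.842 = 2.802 standard errors. If only the SD changes, the effect and r cancel:

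power = Φ(2.802 × (1500/2559) × √(n/349) − 1.960)

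- n = 349: Φ(1.642 − 1.960) = 37.5% (39% with the KAM SD, 36% with the UC SD)
- n = 367, which is 70% of 1049/2: 39.1%
- n = 524, full retention: 52.1%

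Restoring 80% for the same effect would take 349 × 2.91 = about 1,016 evaluable per arm. This shows the size of the gap and is not a request.

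**4. Detectable difference at 80% power, 2.802 × 2 × SD × √((1−r)/n).** The article gives no r, so two values are shown as assumptions.

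| r | SD 1500, n = 349 | SD 2,559, n = 367 |
|---|---|---|
| 0.3 | 376 kcal/wk | 626 kcal/wk |
| 0.67 | 258 kcal/wk | 430 kcal/wk |

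The ratio is 1.71 at equal n, and 1.71 × √(349/367) = 1.66 with the slightly larger n.

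**5. If the actual correlation differs from the planned one.** Power at 350 per arm with SD 2,559:

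| Planned r | Actual 0.3 | Actual 0.5 | Actual 0.67 | Actual 0.8 |
|---|---|---|---|---|
| 0.3 | 38% | 49% | 67% | 87% |
| 0.5 | 28% | 38% | 53% | 74% |

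Power stays at 80% only if actual (1−r) = (1500/2559)² = 0.34 times planned (1−r). A planned r of 0 would need an actual r of about 0.66; a planned 0.3 would need 1 − 0.7 × 0.34 = about 0.76.

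**The case against.** The strongest reply is that the interaction is tested against the SD of change, which baseline data do not show. If planning used a low correlation, a higher actual one would recover some of the loss. A low planned value is plausible under a first-order autoregressive structure: as an illustration, 0.67 between adjacent visits gives 0.67³ = 0.30 across three steps. This stands. A reader might infer that the trial's power really is 38%, but the article states neither the effect nor the correlation and so supports no single figure.

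A reader might also infer that no plausible correlation could offset the larger SD, because the article quotes a six-month ICC of only 0.67. That ICC is for moderate-intensity activities, not total kcal/wk, so it sets no ceiling here. Full recovery needs a marked rise in correlation, but the documents do not exclude one.

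Other points stand in part:

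- Section 2.11 plans a mixed model on all available observations from everyone randomized, not a completers' contrast. The 52% with full retention shows how far fuller data would move the same contrast.
- Section 2.11 drops observations more than 5 SD above the median. Table 2 does not say whether it applies this rule, so the analysed SD could be somewhat smaller. To reach 1500, the variance would have to fall by about two-thirds (1 − 0.34).
- If the effect was planned in SD units, power is unchanged, but the same standardized effect is then about 1.7 times larger in kcal/wk. Section 2.8 states the SD in kcal/wk and mentions no standardized effect.
- Section 2.8 is a past-tense record of planning. A reader might take it as a claim that 80% was achieved; it makes no such claim.
- The unstated effect and autocorrelation are details that a condensed article may leave to the full protocol, and are not in themselves a fault.

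**Conclusion.** The contradiction over the SD holds. Every group shown has a baseline SD between 2,325 and 2,615 kcal/wk, at least 1.55 times the 1500 assumed, and the overall ratio is 1.7. This is a planning assumption that the trial's own data do not bear out; no calculation in the article is shown to be wrong.

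The loss of power is conditional. The fall from 80% to about 38–39% (about 52% with full retention) assumes four things: the planned absolute effect, the planned baseline-to-24-month correlation, a 24-month SD like the baseline one, and little change from the 5-SD exclusion. The actual figure may be higher or lower as the correlation differs from plan. The published 80% should not be relied on for the planned absolute effect unless the condition in step 5 of the working is shown to be met.

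**What to change.** Leave the 1500 kcal/wk assumption in section 2.8 as the historical basis for N. Add a sentence saying that the observed baseline SD of total kcal/wk is about 2,560. Beside it, give either the power for the planned effect or the detectable difference, recomputed with that SD and labelled as conditional on the correlation. Update it with the observed SD of change, after any 5-SD exclusion, once 24-month data are available.

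When reporting, do not interpret a null 24-month interaction against 80% power; rely on the confidence interval for the difference in change.

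The cost is a short addition to one paragraph and a less favourable power statement. Enrolment, design and the planned model are untouched.
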